### **Severity**

The severity of each adverse event must be assessed and recorded on the Adverse Event CRF as mild, moderate, or severe.

|           |                                                                                                                                                                                                        |
|-----------|--------------------------------------------------------------------------------------------------------------------------------------------------------------------------------------------------------|
| Mild:     | An adverse event that is usually transient, requires no special treatment, and does not interfere with usual activities.                                                                               |
| Moderate: | An adverse event that interferes with usual activities but may be ameliorated by therapeutic measures.                                                                                                 |
| Severe:   | An adverse event that is intense or debilitating and that interferes with usual activities. Recovery is usually aided by therapeutic measures and may require the discontinuation of study medication. |

### **Relationship to Study Procedure**

The investigator will assess the relationship between the study medication and the adverse event as probable, possible, unlikely, or unrelated as follows.

|              |                                                                                                                                                                                                                                                                         |
|--------------|-------------------------------------------------------------------------------------------------------------------------------------------------------------------------------------------------------------------------------------------------------------------------|
| Probable:    | Reports including good reasons and sufficient information to assume a causal relationship in the sense that it is plausible, conceivable, or likely.                                                                                                                    |
| Possible:    | Reports containing sufficient information to indicate the possibility of a causal relationship in the sense of it not being impossible and not unlikely, although the connection may be uncertain or doubtful (e.g., due to missing data, insufficient evidence, etc.). |
| Unlikely:    | Reports of a clinical event, including laboratory test abnormality, with a temporal relationship to drug administration which makes a causal relationship improbable, and in which other drugs, chemicals, or underlying disease provide plausible explanations.        |
| Not Related: | Reports excluding the possibility of a relationship between the event and the drug treatment, i.e., no reasonable suspected causal relationship to study medication administration.                                                                                     |

### **6.1.3 Recording Adverse Events**

All adverse events, regardless of relationship to study medication, must be recorded on the Adverse Event CRF. All adverse events reports should contain the date the adverse events occurred, a brief description of the event, time of onset, end date or duration of event (if less than 24 hours), intensity, treatment required, relationship to study medication, action taken, outcome, and whether the event is classified as serious.

### **6.1.4 Follow-Up of Adverse Events**

Reporting of adverse events will terminate on the last day of study follow-up. The investigator must follow non-serious events possibly related to the study medication and all serious adverse events until they resolve or until the investigator assesses them as chronic or stable.

### **6.1.5 Protocol Deviations Due to an Emergency or Adverse Event**

Deviations from the protocol will be determined as allowable on a case-by-case basis. All protocol deviations and the reasons for such deviations must be noted on the CRF.

## **6.2 Schedule of Assessments**

Study outcome measures, The Maslach Burnout Inventory (MBI-HSS) for Medical Personnel, Insomnia Severity Index (ISI), Patient Health Questionnaire (PHQ)-9 depression, Generalized Anxiety Disorder (GAD)-7 and the Warwick-Edinburgh Mental Well-Being Scale (WEMWBS) will be assessed at baseline, 2 weeks, 1 month, and 3 months posttest, (+/- 7 days) with change in burnout as the primary outcome. The measures will either be administered in person or virtually). The total duration of the study period will be 3 months.

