| Objectives/
Endpoints:                              | 
Primary Endpoints:
 
 
1. Burnout: The Maslach Burnout Inventory (MBI-HSS) for Medical Personnel is used to measure participant burnout [15]. The MBI-HSS is a 22-item inventory with a seven-point response scale, measuring emotional exhaustion (9 items), depersonalization (5 items), and personal accomplishment (8 items). Cronbach's alphas range from .76 to .90 (Iwanicki et al., 1981).
 
2. Insomnia: Insomnia Severity Index (ISI) is a 7-item scale, measuring severity of sleep problems. The ISI has satisfactory internal reliability (Cronbach's alpha=.74) (Bastien et al., 2001).
 
3. Symptom: Brief Symptom Inventory 18 (BSI 18) is a 5-point rating scale used to gather patient-reported data to measure psychological distress and psychiatric disorders in medical and community populations. (Derogatis et al, 2001).
 
4. Well-Being: Warwick Edinburgh Mental Well Being Scale (WEMWBS) is a 14-item scale with 5 response categories, summed to provide a single score. The items are all worded positively and cover both feeling and functioning aspects of mental wellbeing, thereby making the concept more accessible. (Tennant et al, 2006).
 
 |

|                                   |                                                                                                                                                                                                                                                                                                                                                                                                                                                                                                                                                                                                                                                                                                                                                                                                                              |

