|-----------------------------------|------------------------------------------------------------------------------------------------------------------------------------------------------------------------------------------------------------------------------------------------------------------------------------------------------------------------------------------------------------------------------------------------------------------------------------------------------------------------------------------------------------------------------------------------------------------------------------------------------------------------------------------------------------------------------------------------------------------------------------------------------------------------------------------------------------------------------|
| Study Design:              | Sixty-five healthcare providers (HCPs) affiliated with the three participating Miami hospitals will be instructed in the Transcendental Meditation Technique as follows: 25 at Baptist Health South Florida Hospital, 25 at Mercy Miami Hospital, and 15 at Encompass Health Rehabilitation Hospital of Miami. A control group of similar numbers of HCPs at each institution will also be recruited, and matched to the best extent possible for gender, age, type of HCP (doctor, nurse, etc.), and work schedule (e.g., days, nights, etc.). Study outcomes will be assessed at baseline, 2 weeks, 1 month, and 3 months' posttest, with change in burnout, insomnia, symptom, and well-being, as measured by the corresponding indexes as the primary outcomes. The total duration of the study period will be 3 months. |

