### **3 OBJECTIVES**

#### **3.1 Primary and Secondary Objectives**

##### Primary Endpoints:

1. Burnout: The Maslach Burnout Inventory (MBI-HSS) for Medical Personnel will be used to measure participant burnout [15]. The MBI-HSS is a 22-item inventory with a seven-point response scale, measuring emotional exhaustion (9 items), depersonalization (5 items), and personal accomplishment (8 items). Cronbach's alphas range from .76 to .90 (Iwanicki et al., 1981).
2. Insomnia: Insomnia Severity Index (ISI). The ISI is a 7-item scale, measuring severity of sleep problems. The ISI has satisfactory internal reliability (Cronbach's alpha=.74) (Bastien et al., 2001).
3. Symptom: Brief Symptom Inventory 18 (BSI 18). The BSI 18 is a 5-point rating scale used to gather patient-reported data to measure psychological distress and psychiatric disorders in medical and community populations. (Derogatis et al, 2001).
4. Well-Being: Warwick Edinburgh Mental Well Being Scale (WEMWBS) is a 14-item scale with 5 response categories, summed to provide a single score. The items are all worded positively and cover both feeling and functioning aspects of mental wellbeing, thereby making the concept more accessible. (Tennant et al, 2006).

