## **7.2 Statistical Methods**

### **7.2.1 General Statistical Methods**

For all primary and secondary outcomes, data will be analyzed using analysis of covariance (ANCOVA). Dependent variable will be change from baseline at three-month post-test, with treatment group as the independent variable, and baseline dependent variable as the covariate. Missing data will be imputed using last observation carried forward (LOCF). Effect sizes will be calculated using Cohen's d: mean differences divided by pooled standard deviation. For the primary outcome, change in total burnout, the significance level will be set at  $p < .05$ , two-tailed. For all secondary outcomes,  $p < .01$ , two-tailed, will be used (to compensate for multiple comparisons).

The primary population for analyses of efficacy data will be ITT population. A supportive analysis will be presented for the PP population if this is significantly different from the ITT population. Continuous data will be summarized by using descriptive statistics (number, mean, median, standard deviation, minimum, and maximum).

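### Section 6.2 schedules PHQ-9 and GAD-7 and does not name the BSI 18, which the synopsis and Section 3.1 list as the symptom endpoint

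*Protocol*

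**What the plan says.** Under a heading for primary endpoints, Section 3.1 of the protocol gives four items. The third is "Symptom: Brief Symptom Inventory 18 (BSI 18). The BSI 18 is a 5-point rating scale used to gather patient-reported data". The synopsis has the same four items and describes the third in nearly the same words: "Brief Symptom Inventory 18 (BSI 18) is a 5-point rating scale used to gather patient-reported data". The other three are the MBI-HSS, the ISI and the WEMWBS.

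The synopsis paragraph on study design sets assessments at baseline, 2 weeks, 1 month and 3 months, "with change in burnout, insomnia, symptom, and well-being, as measured by the corresponding indexes as the primary outcomes". It names no instrument.

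Section 6.2 covers the same four time points and does name instruments. It opens "Study outcome measures, The Maslach Burnout Inventory (MBI-HSS) for Medical Personnel, Insomnia Severity Index (ISI" and goes on "Patient Health Questionnaire (PHQ)-9 depression, Generalized Anxiety Disorder (GAD)-7 and the Warwick-Edinburgh Mental Well-Being Scale (WEMWBS) will be assessed". It closes "with change in burnout as the primary outcome". Section 3.2 also gives burnout alone as primary, and Section 7.2.1 begins its error-rate rule "For the primary outcome, change in total burnout, the significance level will be set at". That rule is p < .05, two-tailed, for total burnout and p < .01, two-tailed, for all secondary outcomes.

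**The concern.** Which questionnaires participants complete is fixed by the protocol and the CRF. No later analysis plan can recover a scale that was not given. If sites take Section 6.2 as their working list, the BSI 18 is not administered, and two scales that no endpoint list mentions are collected in its place.

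Two sites could also follow different parts of the same protocol in good faith and collect different symptom scales. There are three hospitals, so the symptom outcome might then be available in one form at one site and in another form elsewhere. The protocol gives no rule for deriving a BSI 18 score from PHQ-9 and GAD-7.

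If the question is settled only after data are in, the choice of symptom scale is open to the criticism that it was made with the results in view. The outcomes are self-reported, and the comparison is with a matched rather than randomised control group, so that criticism would be hard to answer.

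**Working it through.** The plan states no figure on this point to reproduce. The check is a comparison of lists.

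**Instruments by source**

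| Instrument | Synopsis and Section 3.1 endpoint lists | Section 6.2 schedule |
|---|---|---|
| MBI-HSS | yes | yes |
| ISI | yes | yes |
| BSI 18 | yes | no |
| PHQ-9 | no | yes |
| GAD-7 | no | yes |
| WEMWBS | yes | yes |

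- Endpoint lists: 4 instruments. Schedule: 5. In common: 3.
- Listed but not scheduled by name: 4 − 3 = 1 (BSI 18).
- Scheduled but in no endpoint list: 5 − 3 = 2 (PHQ-9 and GAD-7).

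**Other mentions.** As a study measure, the BSI 18 is named only in the two endpoint lists, and PHQ-9 and GAD-7 only in Section 6.2. No passage links the two sets.

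**Consequence for the analysis.** Section 7.2.1 specifies an ANCOVA of change from baseline at three months, with the baseline value as covariate. Each endpoint therefore needs values at baseline and at three months. If Section 6.2 alone is followed, the BSI 18 has neither. The imputation rules cannot fill the gap. Last observation carried forward (Section 7.2.1) needs an earlier observed value. Replacement by the visit average (Section 7.2.4) needs some non-missing values at that visit.

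**Consequence for multiplicity.** Take burnout as the only primary outcome and count one score per remaining scale. The p < .01 rule then covers k secondary tests, and the Bonferroni bound on the chance of at least one false positive among them is k × .01:

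- ISI, WEMWBS, BSI 18: k = 3, bound 3 × .01 = .03
- ISI, WEMWBS, PHQ-9, GAD-7: k = 4, bound 4 × .01 = .04
- All of these: k = 5, bound 5 × .01 = .05

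The rule itself is the same in all three cases. Only the number of tests under it differs.

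**The case against.** The strongest reply is that the protocol, read as a whole, does schedule the BSI 18. The synopsis design paragraph says the symptom outcome is measured at all four visits by its matching index, and the only index assigned to that outcome is the BSI 18. This is a fair reading. It rules out the stronger conclusion a reader might draw, that the endpoint is never measured if the protocol is followed. It does not remove the problem, because Section 6.2 gives a complete list of named scales for the same visits and the BSI 18 is not among them.

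Three further inferences are tempting and are not supported.

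- *That no participant of the 130 would have BSI 18 data.* This holds only if every site works from Section 6.2 alone. Data are captured on CRFs (Section 7.4), which are not available here.
- *That the trial's primary analysis is lost.* Sections 3.2, 6.2 and 7.2.1 make burnout the only primary outcome, and the MBI-HSS is in every list. On that reading the mismatch touches a secondary outcome. Only the synopsis and Section 3.1 make the BSI 18 primary.
- *That the error-rate rules must change, or that the sponsor means to switch outcomes.* The p < .01 rule applies to all secondary outcomes whatever their number, and nothing in the document points to a planned substitution.

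It may also seem obvious that the BSI 18 is right and Section 6.2 is the slip, since both endpoint lists name it. The reference list points the other way: it holds a psychometric paper on the PHQ-9 and a paper presenting a brief anxiety measure, the GAD-7 source, but not the BSI 18 source cited in the text. That evidence is weak too. The list also lacks the source cited for the WEMWBS, which is in both sets, and it includes papers on scales this protocol does not use. The document does not show which set is current.

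**Conclusion.** The protocol contradicts itself on how the symptom outcome is measured, and nothing in it resolves the contradiction. One of four listed endpoints is absent by name from the schedule, and two of five scheduled scales have no stated endpoint status. If a site follows Section 6.2 alone, the planned ANCOVA cannot be run for the BSI 18 there, and a missed baseline cannot be recovered.

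The loss is conditional on how sites read the document and on what the CRF contains. The burnout analysis does not depend on it. Whether a primary or a secondary outcome is at risk cannot be said, because the protocol disagrees with itself on that as well. It needs correcting because the outcome is a declared one and the remedy costs little. The counts of 3, 4 or 5 secondary tests assume one score per scale and burnout alone as primary.

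**What to change.** Amend the synopsis, Section 3.1, Section 6.2 and the CRF so that all four carry one instrument set. Either the BSI 18 or PHQ-9 plus GAD-7 would do, and the sponsor must choose. State for each scale whether it is primary or secondary, consistently with Sections 3.2 and 7.2.1. The p < .01 rule for secondary outcomes can stay as written, with the number of tests it covers stated.

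This should be done before the first baseline assessment. If enrolment has begun, record which scales were actually given, at which sites and visits, and make the amendment before any analysis.

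The cost is one protocol amendment and a CRF check, with no added participants or visits.

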## **6.3 Study Termination**

If the study sponsor or investigator discovers conditions arising during the study that indicate the study should be halted, the study must be terminated after appropriate consultation between the study sponsor, project manager, and investigator. Conditions that may warrant termination include, but are not limited to, the following – the discovery of an unexpected, significant, or unacceptable risk to the subjects enrolled in the study, insufficient adherence to protocol requirements.

# **7 DATA HANDLING AND RECORD KEEPING**

## **7.1 Archiving Study Records**

Essential documents should be retained on site for a minimum of 2 years after the last approval of a marketing application in an ICH region and until there are no pending or contemplated marketing applications in an ICH region or at least 2 years have elapsed since the formal discontinuation of clinical development of the investigational product. Once the 2 years have elapsed, essential documents will be transferred off site to a secure location and retained for up to 7 years. The documents will be retained for a longer period if required by the applicable legal and regulatory requirements.

## **7.2 Statistical Methods**

### **7.2.1 General Statistical Methods**

For all primary and secondary outcomes, data will be analyzed using analysis of covariance (ANCOVA). Dependent variable will be change from baseline at three-month post-test, with treatment group as the independent variable, and baseline dependent variable as the covariate. Missing data will be imputed using last observation carried forward (LOCF). Effect sizes will be calculated using Cohen's d: mean differences divided by pooled standard deviation. For the primary outcome, change in total burnout, the significance level will be set at  $p < .05$ , two-tailed. For all secondary outcomes,  $p < .01$ , two-tailed, will be used (to compensate for multiple comparisons).

The primary population for analyses of efficacy data will be ITT population. A supportive analysis will be presented for the PP population if this is significantly different from the ITT population. Continuous data will be summarized by using descriptive statistics (number, mean, median, standard deviation, minimum, and maximum).

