| Investigational Procedure: | Transcendental Meditation Technique                                                                                                                                                                                                                                                                                                                                                                                                                                                                                                                                                                                                                                                                                                                                                                                          |
| Subject Population:        | 25 at Baptist Health South Florida Hospital, 25 at Mercy Miami Hospital, and 15 at Encompass Health Rehabilitation Hospital of Miami. A control group of similar numbers of HCPs at each institution will also be recruited, and matched to the extent possible for gender, age, type of HCP (doctor, nurse, etc.), and work schedule (e.g., days, nights, etc.).                                                                                                                                                                                                                                                                                                                                                                                                                                                            |

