#### **3.2 Study Overview**

Sixty-five healthcare providers and hospital administrators (HCPs) affiliated with the three participating Miami hospitals will be instructed in Transcendental Meditation Technique as follows: 25 at Baptist Health South Florida Hospital, 25 at Mercy Miami Hospital, and 15 at Encompass Health Rehabilitation Hospital of Miami. A control group of similar numbers of HCPs at each institution will also be recruited, and matched to the extent possible for gender, age, type of HCP (doctor, nurse, etc.), and work schedule (e.g., days, nights, etc.). Study outcomes will be assessed at baseline, 2 weeks, 1 month, and 3 months posttest, with change in burnout as the primary outcome. The total duration of the study period will be 3 months.

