## **4 STUDY POPULATION**

### **4.1 Inclusion Criteria**

Subjects who meet all of the following criteria are eligible for this study:

- 1) Fulltime healthcare providers, medical doctors, physician assistants, nurses or other HCPs involved in active patient care or administration of patient care (Hospital Administration).
- 2) 18 years or older.
- 3) Have treated COVID-19 patients or working at locations where COVID-19 patients are being treated.
- 4) Willing and able to complete both baseline and post-testing as noted above.
- 5) If being treated with psychoactive medications, the maintenance of a stable regimen for at least two months before enrollment.
- 6) In the non-control group, willing and able to dedicate the time to learning the Transcendental Meditation technique and practice it twice daily for approximately 20 minutes.

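### Controls are matched only as far as possible and no randomisation is described, yet the fixed ANCOVA adjusts for baseline score alone and leaves out every matching factor

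*Protocol*

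**What the plan says.** **Design.** Section 3.2 places TM participants by hospital: "25 at Baptist Health South Florida Hospital, 25 at Mercy Miami Hospital, and 15 at Encompass Health Rehabilitation Hospital of Miami". It then says: "A control group of similar numbers of HCPs at each institution will also be recruited, and matched to the extent possible for gender, age", and goes on to type of provider and work schedule. The synopsis has controls "matched to the best extent possible for gender, age, type of HCP (doctor, nurse, etc.), and work schedule". No allocation procedure is described for this study; randomisation appears only in the Introduction's accounts of earlier trials. One eligibility criterion in Section 4.1 applies to the TM arm only: "In the non-control group, willing and able to dedicate the time to learning the Transcendental Meditation technique".

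**Analysis.** Section 7.2.1 names ANCOVA for all primary and secondary outcomes. The response is change from baseline at three months, "with treatment group as the independent variable, and baseline dependent variable as the covariate". There is no term for gender, age, type of provider, work schedule, site or matched set. Section 7.2.6 breaks demographics down by treatment and age group, but only descriptively. No other section adds adjustment.

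**The concern.** The design and analysis sections do not fit together. The design names four factors important enough to match on and concedes that the match will be partial. The analysis then uses none of them.

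In a randomised trial this would cost only precision. Here the arms are formed by recruitment, so a difference in shift pattern or professional mix that survives matching can carry over into the estimated TM effect. This model produces the primary result, change in total burnout, tested at two-sided 0.05. A systematic shift in the estimate makes that nominal error rate too low. If the matching works well, the loss is different: the standard error is wider than it needs to be wherever the factors predict outcome.

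**Working it through.** **1. The plan's own figure.** The only relevant number is the sample size: 2 × (25 + 25 + 15) = 130, which agrees with Section 7.2.2. No effect size, SD or power is given, so it cannot be reproduced as a power calculation.

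**2. Inputs.**
- From the protocol: 65 per arm; two-sided 0.05; model with group and baseline, so 130 − 3 = 127 residual degrees of freedom.
- Assumed, because the documents give none of them: D, the difference between arms in the prevalence of a binary factor; g, its effect in outcome SDs; a baseline to follow-up correlation of 0.6, which gives a residual SD of √(1 − 0.6²) = 0.8.

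**3. Formulas.** Two cases bound the bias when the factor is left out:
- The factor acts entirely beyond baseline: bias = D × g.
- The factor shifts baseline and follow-up equally, so ANCOVA absorbs part of it: bias ≈ D × g × (1 − 0.6).

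The noncentrality is bias / (0.8 × √(2/65)) = (bias / 0.8) × 5.70. The false-positive rate comes from the noncentral t with 127 degrees of freedom.

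**4. Results with no true effect.**

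| Assumed residual imbalance | Case | Bias (SD) | Noncentrality | Type I error |
|---|---|---|---|---|
| One factor, D = 0.20, g = 0.5 | equal shift | 0.20 × 0.5 × 0.4 = 0.04 | 0.285 | 5.9% |
| One factor, D = 0.20, g = 0.5 | beyond baseline | 0.20 × 0.5 = 0.10 | 0.713 | 10.9% |
| Two such factors, same direction | equal shift | 2 × 0.04 = 0.08 | 0.570 | 8.7% |
| Two such factors, same direction | beyond baseline | 2 × 0.10 = 0.20 | 1.425 | 29.3% |
| One factor, D = 0.10, g = 0.5 | equal shift to beyond baseline | 0.02 to 0.05 | 0.143 to 0.356 | 5.2% to 6.4% |
| One factor, D = 0.05, g = 0.5 | beyond baseline | 0.025 | 0.178 | 5.4% |

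**5. Check by simulation** (20,000 runs per row, factor prevalence centred on 50%). For one factor at D = 0.20 and g = 0.5, the stated model gave bias 0.037 and error 5.9% under equal shift, and bias 0.099 and error 10.3% beyond baseline. For two factors it gave 0.071 and 8.1%, and 0.201 and 25.5%. The last figure is below 29.3% because an omitted factor also inflates the residual variance: 0.64 + 2 × 0.24 × 0.25 = 0.76, an SD of 0.87 instead of 0.8. With the factor or factors in the model, bias was about zero and error stayed near 5% throughout. With D = 0 the stated model was unbiased, with error 4.9–5.1%.

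**6. Precision.** If the factors explain 10% or 20% of residual variance (assumed), the standard error is multiplied by √0.90 = 0.949 or √0.80 = 0.894. Power for a difference of 0.4 SD goes from 81% to 85% or 89%.

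**The case against.** **Baseline adjustment and matching already protect.** A stable trait such as gender or usual shift will normally move the baseline burnout score too, and ANCOVA then removes part of its effect. This stands. A reader might infer that adjustment for further covariates is the only analytic safeguard, or that any imbalance passes in full into the TM effect. The documents do not support that: the baseline term is itself a safeguard, and the full bias arises only if the factor changes the course of burnout beyond baseline.

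**The highest error rates are stacked assumptions.** The 25–29% needs two matched factors, each still 20 points out, both in the same direction, each worth 0.5 SD beyond baseline. Nothing in the protocol makes that the expected case.

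**Site is not a confounder of the same kind.** One might list site among the unadjusted confounders. However, the synopsis provides that "A control group of similar numbers of HCPs at each institution will also be recruited", so site is roughly balanced by design. Leaving it out costs mainly precision.

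**The remedy misses the clearest selection difference.** Inclusion criterion 6 requires willingness to learn and practise TM in the TM arm only, and no matching factor measures that. This stands as a limit on the remedy. It is not a reason to leave measured factors out.

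**A statistical analysis plan may add covariates.** Section 8.2 refers to one, which is not shown. But the protocol names both the model and its single covariate, so this is a stated specification and not an open detail.

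**The precision gain is only efficiency.** True: a wider standard error is conservative, and the variance shares are assumed.

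**Conclusion.** The point holds in a limited form. The protocol fixes a primary model that ignores the four factors its design tries, only partly, to balance. Residual imbalance can therefore bias the TM effect, and available precision goes unused.

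For one factor 20 points out and worth 0.5 SD, the bias is about 0.04 to 0.10 SD and the true error rate about 5–6% to 10–11%. Two such factors in the same direction give about 8% to 25–29%. At imbalances of 5–10 points the effect is negligible, and with matching that is exact on average there is no bias from these factors. All of this rests on assumed imbalances, factor effects and a 0.6 correlation, none of which the documents supply.

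It would be wrong to infer that the planned result must be biased, or that adding the factors would make the comparison equivalent to a randomised one.

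**What to change.** In Section 7.2.1, state the primary model as: change = group + baseline outcome + gender + age (continuous) + type of provider + work schedule, plus site (three levels) mainly as a precision term. The sponsor should set the provider and schedule categories before analysis and say where hospital administrators, who are eligible, are placed. Keep the baseline-only ANCOVA as a sensitivity analysis.

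Add one sentence saying that adjustment for measured factors does not remove confounding by willingness to learn and practise TM, which inclusion criterion 6 requires in one arm only.

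**Cost.** This is a wording change; the four factors must be known to do the matching, and site is known. With, for example, three provider and two schedule categories, the added terms use 1 (gender) + 1 (age) + 2 (provider) + 1 (schedule) + 2 (site) = 7 of 127 residual degrees of freedom, leaving 120. Fixing the covariates now also prevents their being chosen after the data are seen.
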